### Interventions

#### ​Training and monitoring of intervention delivery

The best-practice advice and progressive functional exercise interventions will be provided face-to-face and one-to-one by physiotherapists. The study team will give the treating therapists training and an intervention manual on the theory and practical delivery of the interventions. Treating physiotherapists will record the delivery and content of the sessions attended by each participant.

Patient pathways vary at different hospitals so patients may have had instruction on basic ankle exercises, wound care and use of walking aids from a physiotherapist or other health professional while an inpatient or in an acute fracture clinic before starting the study interventions. This will be recorded in the study treatment log. The intervention session(s) can be tailored to the patient’s recovery level, as per usual care. Some centres make referrals for physiotherapy while patients are inpatients or at earlier clinic follow-ups. Other centres delay referrals until a clinic review several weeks later. The study will adapt screening and recruitment to embed in the patient pathway as much as is practical. The process at each centre will be reviewed as the study progresses.

The best-practice advice or progressive functional exercise sessions will be given when the participant can mobilise with unrestricted weight-bearing and do ankle exercises as guided by their surgeon or physiotherapist. We anticipate that this will usually be around 6 to 8 weeks post-injury.

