Healthcare use	NHS outpatient and community services (eg, general practitioner, additional physical therapy) NHS inpatient and day case (eg, radiography, readmissions) Private healthcare services	3 and 6 months
Out-of-pocket expenses	Patient-related out-of-pocket expenses recording form	3 and 6 months
Adverse events	Patient-reported adverse events	3 and 6 months

NHS, National Health Service.

Patient-reported outcomes at 3 and 6 months will be:

ankle-related symptoms and function: Olerud and Molander Ankle Score^38^
lower-limb function limitations: Lower Extremity Functional Scale^39^
pain: Visual Analogue Scale, 0 to 100 scale health-related quality of life: EQ-5D-5L score^40^
fear of falls: Falls Efficacy Scale-International (short version)^41^
self-efficacy: self-efficacy exercise score^42^
return to desired activities, including work, social life and sport activitieswalking aid use and distancesexercise adherence

At 6 month follow-up, a blinded outcome assessor will collect objective measures of ankle function and physical performance:

ankle joint range: hand-held goniometry^43^
muscle strength: hand-held dynamometry (Lafayette Manual Muscle Test System, Lafayette Instrument, Indiana, USA) of ankle dorsi/plantarflexion using a ‘make’ approach (working up to a maximal contraction over a maximum of 5 s and without pushing into pain and the assessor maintaining position of the device).^44^ Participants will be measured three times and have at least 10 s rest between attempts. Self-reported body weight will be recorded to aid interpretation of strength measures.mobility and balance: short physical performance battery.^45^ The test involves physical tests of balance, walking speed and repeated rises from a chair. It has been used extensively in clinical trials owing to its practical utility, the strong evidence base for its measurement properties, and its relationship to frailty, risk of falls and disability in older adults.^46^

Data on health resource use (consultation with primary and secondary care, prescribed and over-the-counter medication use, additional physiotherapy and hospital admission), additional out-of-pocket expenses and work absence (number of sickness days) will also be collected to inform a future definitive RCT. A full health economic evaluation will not be conducted. Data will be collected alongside the other outcome measures in participant questionnaires.

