#### ​Adverse events

Foreseeable adverse events (AE) occurring as a result of the trial intervention(s) will be recorded. Participants will receive information on the potential AEs resulting from the treatment exercises and what they should do if they experience an AE, as would happen as part of standard NHS procedures.

Expected general side effects of any exercise, such as delayed-onset muscle soreness and temporary increases in pain <1 week, will not be recorded as AEs. Pain increases >1 week will be recorded in patient-reported questionnaires. Although unlikely, any exacerbations of other medical conditions during exercise or exercise-related injurious falls will be recorded in patient-reported questionnaires or by the site investigators if they become aware of such an event.

A serious AE (SAE) is any unexpected untoward medical occurrence related to the trial interventions that results in death, is life-threatening, requires inpatient hospitalisation or prolongation of existing hospitalisation, or results in persistent or significant disability/incapacity. SAEs are likely to be rare and are unlikely to occur as a result of the exercise programmes delivered in this study. If an SAE arises between study enrolment and final follow-up visit and is deemed related to the trial interventions, the Clinical Trials Unit standard operating procedures will apply.

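### Harms from the 6-month physical tests fall outside the AE and SAE definitions and have no scheduled later collection point

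*Protocol article*

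**What the plan says.** The Adverse events section sets the scope by cause. For AEs: "Foreseeable adverse events (AE) occurring as a result of the trial intervention(s) will be recorded". For SAEs: "A serious AE (SAE) is any unexpected untoward medical occurrence related to the trial interventions", with the usual seriousness criteria added. Clinical Trials Unit procedures are then invoked under this condition: "If an SAE arises between study enrolment and final follow-up visit and is deemed related to the trial interventions". On pain, increases of less than 1 week are not counted as AEs, and for longer ones "Pain increases >1 week will be recorded in patient-reported questionnaires". Site investigators may also record injurious falls related to exercise, and exacerbations of other conditions during exercise, if they learn of them.

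The section on training and monitoring of intervention delivery makes clear what the interventions are: "The best-practice advice and progressive functional exercise interventions will be provided face-to-face and one-to-one by physiotherapists".

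The Outcomes section describes a different activity: "At 6 month follow-up, a blinded outcome assessor will collect objective measures of ankle function and physical performance". The strength test involves "working up to a maximal contraction over a maximum of 5 s and without pushing into pain", measured three times. Of the short physical performance battery it says "The test involves physical tests of balance, walking speed and repeated rises from a chair".

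Table 2 schedules patient-reported adverse events at 3 and 6 months. Table 1 shows no contact after 6 months.

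**The concern.** Participants are aged 50 or over and are recovering from an ankle fracture. At 6 months those who attend are asked for maximal ankle efforts, balance tasks and repeated chair rises that are not part of either treatment. If someone falls, has to stop, or has a prolonged pain flare because of these tests, the cause is a trial assessment and not a trial intervention.

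This matters because the pilot has four main objectives and one is the acceptability of measuring outcomes at 3 and 6 months. The Outcomes section says the measures are collected to learn whether they can feasibly be collected in the definitive trial. Falls, stopped tests and flares are direct evidence on that question. The Statistical analysis section reports AEs and SAEs, and the trial management group reviews them (Ethics and dissemination). An event outside both definitions has no assured route to either.

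**Working it through.** There is no figure to reproduce. The check sets the definitions, the schedule and the assessments side by side.

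1. **Does a test-related harm meet the AE definition?** The definition requires the event to result from a trial intervention. The interventions are best-practice advice and progressive functional exercise. Goniometry, dynamometry and the physical performance battery are listed as outcome measures and carried out by a blinded assessor, whereas physiotherapists deliver the interventions. The harm does not meet the definition.

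2. **Does it meet the SAE definition?** The same causal link is required, so it does not. The referral to Clinical Trials Unit procedures does not repair this, because it takes effect only once an event has been judged related to the interventions.

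3. **Does the site-investigator route cover it?** Only in part. That route names injurious falls related to exercise and exacerbations of other conditions during exercise. Read in context, the exercise meant is the treatment exercise, although a generous reader could include chair rises and balance tasks. It does not name ankle pain, a fall without injury or a stopped test. It depends on the investigator becoming aware, and no end date is given for it.

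4. **Is there a later collection point?** The SAE window runs to the final follow-up visit, without saying whether that day is included. The last AE questionnaire is due at 6 months. The Follow-up data collection section allows reminders, and telephone or electronic completion of missing core items, but schedules no new contact.

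5. **Can pain provoked at the visit reach the recording threshold?** It must last more than 7 days and is recorded by questionnaire. A questionnaire completed at the visit comes 0 days after the tests. A late questionnaire could capture such pain by chance, not by design.

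6. **Could the interviews fill the gap?** The Embedded qualitative study section places them about 4 months after randomisation, before the 6-month tests have taken place.

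Steps 1 and 2 establish the gap in the definitions. Steps 4 and 5 establish the gap in scheduled collection. Step 3 shows that neither gap amounts to a bar on recording.

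**The case against.** The strongest reply is that this is a journal article. Handling of incidents during assessments, case report form fields and the exact end of the reporting window are often left to a full protocol and unit procedures that are not shown. That stands for forms and procedures, and the gap is shown only for this article. It does not dispose of the causal scope, which the article states outright and too narrowly for what it asks participants to do.

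A second reply is that the tests carry safeguards: efforts stop short of pain, contractions last at most 5 s with at least 10 s of rest, and the battery is described as widely used in trials. This is fair and suggests that events will be few. It does not decide where they are recorded.

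A third is that every fixed follow-up has an edge, so pain starting just before the last visit is always missed. That is correct for treatment-related pain, particularly as Table 1 places the supervised sessions in months 0 to 4. The tests differ because the exposure occurs at the edge itself.

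Some stronger readings should be resisted:

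- A reader might infer that test harms cannot be recorded at all, or that the pilot is bound to report none. The documents do not support this. Events at the visit happen in front of study staff, the window may include that day, the site-investigator route has no end date, and refused or stopped tests may show up as incomplete data.
- A reader might assume that the injured side is tested. The article names no side.
- A reader might take fear of falling as documented in these participants. The Introduction reports it from another trial, in people aged 60 and over.

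**Conclusion.** The point holds as a gap in definition and in scheduled collection. Harms caused by the 6-month physical tests fall outside both stated definitions, and no scheduled contact follows the visit at which the tests are done. Chance capture remains possible, so the consequence is incomplete evidence and not a guaranteed absence of reported harm.

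The size is modest. None of the four success criteria, the sample size or the treatment comparison depends on it. It bears on one main objective and on safety review of a research procedure. It concerns only participants who attend in person, since remote follow-up is offered to those who cannot.

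The conclusion assumes that the interventions mean the two physiotherapy programmes, as the article uses the term throughout, and that the full protocol does not already widen the scope.

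**What to change.** In the Adverse events section:

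- Extend relatedness, for both AEs and SAEs, to cover trial assessments as well as trial interventions.
- State that the collection window includes the final follow-up visit.
- Have the 6-month assessor log any fall, stopped test or pain at the visit.
- Report these events under the objective on acceptability of measuring outcomes.

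Optionally, add one brief text or call more than 1 week after the visit, using the telephone and SMS routes already in the Follow-up data collection section. This is the only step that would reliably capture pain meeting the protocol's own duration threshold.

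The cost is a small wording amendment and one field on the visit form. The optional contact adds one message or call per attender, at most 60 because recruitment is capped at 60, and closes follow-up slightly later. Eligibility, treatment and the success criteria are untouched.

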#### ​Follow-up data collection

Participants will be followed-up 3 months after randomisation with a postal questionnaire and 6 months after randomisation face-to-face at the hospital. They will be offered telephone, postal or electronic follow-up if they are unable to attend the 6 month follow-up.

Participants will be asked to complete the 3 month (and, if applicable, 6 month) questionnaire(s) and return it to the AFTER trial team. Those who do not respond to the initial questionnaire will be sent at least one reminder by telephone, SMS text messaging or email. Telephone and electronic follow-up will also be used to collect a core set of questionnaire items if these are not completed on the returned questionnaire.

#### ​Sample size

The main feasibility objective and therefore the basis of the sample size estimate is participant recruitment at three centres with a staggered start. The target sample size is a minimum of 48 participants. Based on three sites and staggered starts, this is equivalent to at least 1.5 participants per month per site over 12 months. This sample size will enable an estimate of a minimum 25% recruitment rate of those eligible to within a 95% CI of ±6% (calculated using the modified Wald method).^47^ If the sample size is achieved sooner than 12 months, recruitment will continue up to a maximum of 60 participants to enable further feasibility assessment regarding the change to the best practice advice intervention. Recruitment will cease if the target minimum sample size is not achieved within 18 months. We have selected a conservative recruitment rate as recruitment to previous ankle fracture exercise trials in younger adults with less complex health needs has been 37% to 80%.^20 21^

#### ​Statistical analysis

Feasibility outcomes will be reported, including the number of participants who are approached, are eligible, consent to randomisation and are followed-up, attendance of intervention sessions, completion rates of exercise diaries and data completeness. Baseline characteristics will be reported using descriptive statistics, per group and overall, using mean and SD (or median and IQR if non-normally distributed), and minimum and maximum, for continuous variables and number and percentage of patients in each group for binary or categorical variables.

Clinical outcome measures will be reported descriptively. Differences between treatments for the intention-to-treat population will be reported with 95% CIs. Withdrawals from treatment and the trial will be reported, with reasons where provided. AEs, and SAEs will be reported, both the number of participants that experience an event and the total number.

The primary statistical analysis will be carried out on the basis of intention-to-treat, with all randomised participants included and analysed according to their allocated treatment group, irrespective of which treatment they actually receive or their treatment compliance.

#### ​Embedded qualitative study

Investigating patient experience is fundamental to understanding how interventions affect patients’ lives and will give insights into the acceptability of the trial interventions and randomisation to them. The embedded qualitative study aims to find out more about the patients’ experience of the two interventions within the context of their recovery from ankle fracture. This understanding will help us review the acceptability of the two interventions, which aspects help or hinder recovery. This will enable us to refine the interventions, retaining aspects that are important to patients and developing or removing those that are less helpful. For instance, patients may struggle with the pace or complexity of the progressive exercises, which could then be modified for the future definitive trial. In addition the interviews will provide valuable insight into how patients experience the trial processes. For example we know that patients take part in studies because they place their trust in the clinical team, they can have trouble understanding some information, can find randomisation unacceptable in clinical situations and have therapeutic misconceptions.^48–50^ Gaining an insight into the aspects that facilitate and limit participation in the study will help us refine our information processes to include areas that are of concern to patients.

Interviews will be undertaken with a purposive sample of up to 20 participants from recruiting centres and each intervention group, approximately 4 months after randomisation. Participants will be invited to take part and provide their agreement to be contacted for an interview after they have consented to the main pilot trial. Written informed consent will be provided prior to the interview. The interviews will provide an insight into patient experience of being in the trial, the interventions and recovery and outcomes that are important to them within the context of their life. Factors that inhibit or facilitate their ability to fully take part in the study will be used to inform a large-scale definitive RCT.

To sensitise the research team to factors that are important to study participants the semi-structured interview schedule will be informed by input from a PPI member and a therapist. Open questions will be used to ensure participants can talk freely about what is important to them. Participants will choose whether to be interviewed in the local hospital, over the telephone or at home.

The experiences of therapists delivering the trial interventions and recruiting patients will also be explored. Therapists will be invited to participate in a focus group to be held at the end of the recruitment phase.

Interviews and the focus group will be audio-recorded, transcribed verbatim and NVivo (QSR International Pty Ltd, Melbourne, Australia) will be used to help manage the data. Data will be coded and grouped into categories and themes drawing on thematic analysis.^51^ Any quotes used in reporting of the findings will be anonymised.

### Patient and public involvement

The development of the study funding application, intervention development and study materials were supported by a patient and public involvement group, who will also be involved in developing the dissemination strategy.

## Ethics and dissemination

The AFTER study has been prospectively registered. All protocol amendments will be subject to review by the Sponsor (Oxford University), the ethics committee and Health Research Authority and will be included in the final report. All data will be processed following Oxford Clinical Trials Research Unit standard operating procedures. Adverse events and serious adverse events are likely to be rare. If they occur they will be reviewed by the trial management group.

This protocol has been reported following the Standard Protocol Items: Recommendations for Interventional Trials (SPIRIT) statement.^52^ Results will be published in an open-access journal, reported following the Consolidated Standards of Reporting Trials (CONSORT) guidelines for pilot and feasibility trials.^53 54^ The Template for Intervention Description and Replication (TIDieR) statement will be used to report the intervention,^55^ ensuring replication is possible. Results will be published in a peer-reviewed journal with authorship eligibility according to the International Commitee of Medical Journal Editors (ICMJE) criteria. Participants will be asked if and how they would like to be informed of the study results during the consent process. We will share study results before publication with those participants who request it.
